### HbA1c

In all secondary analyses involving HbA1c, the venous HbA1c value will be used at baseline, 6 months, 12 months, and 24 months. At all other time points, the capillary HbA1c value will be used instead.

During the extension phase, HbA1c will be measured by the central lab at 36 and 48 months. At all other time points, local HbA1c will be measured instead.

### CL System Use (in the CL arm only)

CL system use will be calculated using logs generated by the control algorithm. Any temporary basal insulin rate lasting less than 30 minutes will be considered to indicate system being in CL.

## 5 Description of Statistical Methods

### 5.1 General Approach

This is an open-label, multi-center, single-period, randomized, parallel group design study of participants aged 10 to <17 years. It is expected that a total of up to 190 subjects will be recruited within ten working days of diagnosis of type 1 diabetes (T1D) through pediatric diabetes centers in the UK. Half of the participants will be treated by conventional multiple daily injection therapy (MDI) and the other half by closed loop insulin delivery system (CL). Initiation of treatment arm occurs at study visit 5 and will last 24 months. Additionally, subjects will have the option to participate in an extension phase that will go until 48 months.

The study includes up to 14 visits and 1 telephone/email contact for subjects completing the study. For subjects completing the extension phase, it will include an additional 3 visits and 6 contacts. After initiation of the treatment arm, visits will be conducted every 3 months in both arms during the main study and the optional extension phase. Beta-cell function will be assessed by serial measurement of C-peptide in response to a standardized MMTT. MMTTs will be conducted at baseline, 6, 12, and 24 months post diagnosis.

All analyses will compare the CL arm with the MDI arm and will follow the intention-to-treat principle with each participant analyzed according to the treatment assigned by randomization regardless of actual CL utilization. All randomized participants who have at least one CGM reading during the 24 month study period will be included in the secondary analyses of CGM metrics. For secondary analyses of CGM metrics after 24 months, only subjects with at least one reading occurring during the extension phase (i.e. after the date of the 24 month visit) will be included. The primary analysis will include all randomized participants.

All covariates obtained on a continuous scale will be entered into the models as continuous variables, unless it is determined that a variable does not have a linear relationship with the outcome. In such a case, categorization and/or transformation will be explored. All p-values will be two-sided.

Standard residual diagnostics will be performed for all analyses. If values are highly skewed, then an alternate transformation or nonparametric methods will be used instead for the primary outcome. Previous experience suggests that a transformation or nonparametric analyses may be necessary for the hypoglycemic and hyperglycemic outcomes. We do not expect that a transformation or nonparametric analyses will be necessary for HbA1c or some CGM metrics for assessing overall glucose control (such as mean glucose or percent time-in-range).

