#### *HbA1c Outcomes*

- 2) HbA1c levels at 24, 36, and 48 months

F:\user\Diabetes Studies\JDRFAPP\Protocols\APCam Newly Diagnosed - CLOuD\Statistics\Electronic Binder\4. SAP\CLOuD SAP V2.0 4-4-19.docx

- 47 3) Percentage of patients in each group with HbA1c <7.5% (58 mmol/mol) at 12, 24, 36,  
48 and 48 months

49 *CGM Outcome Metrics*

50 Overall Glucose Control

- 51 4) Percentage of time spent with sensor glucose in the target range (3.9 to 10 mmol/L) at  
52 24, 36, and 48 months  
53 5) Mean of glucose levels  
54 6) Standard deviation of glucose levels  
55 7) Coefficient of variation of glucose levels

56 Hyperglycemia

- 57 8) Percent Time spent with glucose levels above 10.0 mmol/L  
58 9) Percent Time spent with glucose levels above 16.7 mmol/L

59 Hypoglycemia

- 60 9) Percent Time spent with glucose levels below 3.9 mmol/L at 24, 36, and 48 months  
61 10) Percent Time spent with glucose levels below 3.5 mmol/L  
62 11) Percent Time spent with glucose levels below 3.0 mmol/L  
63 12) Percent Time spent with glucose levels below 2.8 mmol/L  
64 13) Area under the curve of glucose levels below 3.9 mmol/L  
65 14) Area under the curve of glucose levels below 3.5 mmol/L

66 *Insulin Delivery*

- 67 15) Total insulin dose (U/day/kg)  
68 16) Basal insulin dose (U/day/kg)  
69 17) Bolus insulin dose (U/day/kg)

70 *Weight*

- 71 18) Change in body mass index (BMI) standard deviation score

72 *Blood Pressure*

- 73 19) Systolic blood pressure  
74 20) Diastolic blood pressure

75 *Lipid Profile*

- 76 21) Total cholesterol  
77 22) Triglycerides  
78 23) HDL cholesterol  
79 24) LDL cholesterol

80 \*All secondary endpoints will be compared between treatment groups at 12 and 24 months post  
81 diagnosis of T1D. Additionally, secondary endpoints will be compared at 36 and 48 months for  
82 subjects who opt to enroll in the extension phase of the study.

83

84 **4.1 Calculation of the Primary Outcome**

85 For each mixed meal tolerance test (MMTT), the baseline C-peptide value will be defined as the  
86 mean of measurements taken at -10 and 0 minutes. If one of these measurements is missing, then  
87 the other one will be used as baseline. In the calculation, the starting time of the MMTT will be  
88 defined as t=0 if the C-peptide value is available at that time point. Otherwise, it will be set to t=-  
89 10.

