## 7.3 Regression Modeling

At 12 months post diagnosis, a longitudinal analysis will be conducted for the primary outcome and each continuous secondary outcome using a linear mixed model with a random intercept and slope. For binary outcomes, a repeated measures logistic regression model will be used. All data collected up to and including the 12 month visit will be used to fit the models. The models will account for repeated measures coming from the same subject using an unstructured covariance matrix. They will adjust for baseline value, gender, presence or absence of DKA at diagnosis, and age as fixed effects, in addition to site as a random effect. If necessary, they may also adjust for HbA1c levels, BMI z-score, or race/ethnicity to assess for the presence of confounding. Residual values will be examined for an approximate normal distribution. If values are highly skewed, then a transformation or non-parametric methods will be used instead.

Using these longitudinal models, one treatment arm comparison will be performed specifically at 12 months for each metric and another treatment arm comparison will be performed combining data over all follow-up visits. The latter will be calculated using a linear contrast giving equal weight to each follow-up visit.

A composite analysis will not be performed for the lipid profile metrics, because they are not collected at any time points between the baseline visit and the 12 month visit (see table above).

An analogous longitudinal model will also be run at 24 months for each outcome metric, and at 36 and 48 months for subjects who participated in the extension phase.

In addition to the longitudinal models, boxplots will be used to display the distributions of the primary and secondary outcomes over time. If the longitudinal model produces a significant composite p-value for a particular outcome, then the boxplots will be used to explore the time at which the outcome began to differ between treatment arms.

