#### 7.5 Missing Data

In the event that a particular outcome metric is unavailable at 12, 24, 36, or 48 months but data is available at previous time points, it will be estimated using the method of direct likelihood described in section 6.3.1. This method will be applied to all applicable secondary outcomes.

In the HbA1c analyses, the primary outcome will be venous HbA1c, and capillary HbA1c will be treated as an auxiliary variable.

Missing CGM data will not be imputed in this study.

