6. Number of any other serious adverse events reported per subject

Comparison of safety outcomes between the two treatment groups only include those events occurring on or after randomization until the last visit date or the last event date (whichever is later). Comparisons will be performed at 12 and 24 months post diagnosis of T1D. For subjects who continue into the extension phase, comparisons also will be done at 36 and 48 months.

For the binary safety outcomes listed above, a repeated measures logistic regression model will be used to compare treatment arms. For the count outcomes and the incidence rates, a Poisson regression model will be used. All models will adjust for site as a random effect. Additionally,

F:\user\Diabetes Studies\JDRFAPP\Protocols\APCam Newly Diagnosed - CLOuD\Statistics\Electronic Binder\4. SAP\CLOuD SAP V2.0 4-4-19.docx

the models for the DKA outcomes will adjust for presence of a DKA event at diagnosis. A p-value <0.05 will be used to declare statistical significance.

Any other adverse events will be listed by treatment group.

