## 9.13 Transition to usual care

Following visit 14, for those not wishing to continue in the extension phase, (or following Visit 17 for those completing the extension phase) subjects randomised to closed loop will revert to conventional insulin therapy by switching back to either insulin pump alone or multiple daily injection therapy as per decision of the clinical team. Refresher training sessions on standard therapy will be provided by the routine clinical team to facilitate transition to usual care over a period of up to 8 weeks. During this period, subjects will be able to continue using the study insulin pump and/or study CGM (but not closed-loop) as required to facilitate transition. Subjects of the control intervention will continue with standard therapy as before.

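### The 36- and 48-month comparisons are limited to participants who chose the extension, which conflicts with the stated intention-to-treat principle and risks selection bias

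*Combined protocol and SAP*

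**What the plan says.** The restriction appears in four places in the SAP.

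- Section 5.1, on CGM outcomes beyond month 24: "only subjects with at least one reading occurring during the extension phase (i.e. after the date of the 24 month visit) will be included".
- Section 7.3, for the longitudinal models: they are run at 24 months for each outcome, "and at 36 and 48 months for subjects who participated in the extension phase".
- Section 4, footnote to the endpoint list: "secondary endpoints will be compared at 36 and 48 months for" those who opt to enrol in the extension.
- Section 8, for safety, for those who "continue into the extension phase, comparisons also will be done at 36 and 48 months".

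Other text points the other way. SAP 5.1 says that all analyses "will follow the intention-to-treat principle with each participant analyzed according to the treatment assigned by randomization". Protocol 14 says that all randomised participants are included. SAP 5.2 admits to the CGM analyses every randomised participant with at least one reading and makes no exception after month 24. SAP 7.5 applies direct likelihood "In the event that a particular outcome metric is unavailable at 12, 24, 36, or 48 months but data is available at previous time points".

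On entry, Protocol 9.14 makes the extension optional and requires fresh consent. Under Protocol 9.13, when participants do not continue, "subjects randomised to closed loop will revert to conventional insulin therapy by switching back to either insulin pump alone or multiple daily injection therapy", while control participants continue standard therapy unchanged.

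**The concern.** Whether to enter the extension is decided after randomisation, with the arm known and with two years' experience of it. The incentive is unequal, because declining ends closed loop in one arm and changes nothing in the other. If entry depends on how participants have fared, and does so differently by arm, the entrants are no longer comparable groups, and adjusting for baseline does not fully restore comparability.

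What is at stake is the extension's own question (Protocol 5.3): fasting C-peptide with glucose, HbA1c and CGM measures at 36 and 48 months. Leaving non-entrants out also discards their data to month 24, which are the data that could explain who left. No sensitivity analysis for selective entry is planned.

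**Working it through.** **1. Does the plan exclude non-entrants?** SAP 7.5 describes a non-entrant exactly: no value at 36 or 48 months, but earlier values present. SAP 5.1 and 7.3 remove that person before the model is fitted. Both cannot govern the same analysis, so the passages need reconciling.

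**2. The plan's own figure.** The documents give no sample size, power or opt-in rate for the extension. The 12-month calculation (SAP 3: effect 0.126, SD 0.18, 90% power, two-sided 0.05) sets the scale:

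2 × (1.960 + 1.282)² × (0.18/0.126)² = 42.9 per arm.

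The exact t calculation first reaches 90% at 44 per arm (90.09%), which matches the SAP. Step 4 uses 44 per arm.

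**3. Size of the bias in large samples.** Assumptions, none from the documents:

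- no true effect and standardised values;
- correlation 0.7 between the 24- and 48-month values;
- closed-loop opt-in 90% at random;
- control opt-in 50-79%, with log-odds rising by 0.5 to 1.0 per SD of the 24-month value.

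Let m be the mean 24-month value among control entrants, in SD.

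- Unadjusted difference = −0.7m. Simulation gives −0.07 to −0.29 SD, so m runs from 0.07/0.7 = 0.10 to 0.29/0.7 = 0.414.
- SAP 7.3 adjusts for baseline. If baseline correlates r with both later values, control entrants' baseline mean is shifted by r·m and the adjustment removes about r × r·m. The remaining bias is about −m(0.7 − r²).
- r = 0.3: 0.10 × 0.61 = 0.06, up to 0.414 × 0.61 = 0.25 SD.
- r = 0.7: 0.10 × 0.21 = 0.02, up to 0.414 × 0.21 = 0.09 SD.

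Direct simulation with a baseline covariate agrees: about 0.02 to 0.25 SD in absolute size. The sign reverses if it is the controls with lower values who stay. The likelihood estimate using all randomised participants' data to month 24 stays within 0.004 SD of zero.

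**4. Behaviour at trial size.** 44 per arm, 4,000 runs per setting, no true effect, values at baseline, 12, 24 and 36 months, average opt-in about 67-70% (assumed). Entries are for equal correlation 0.5 / 0.7, with bias in SD. Both analyses adjust for baseline.

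| Opt-in depends on | Extension-only bias | Type I error | All-randomised bias | Type I error |
|---|---|---|---|---|
| Nothing (random) | 0.00 / 0.00 | 5.0% / 4.7% | 0.00 / 0.00 | 4.8% / 4.7% |
| 24-month value, same in both arms | 0.01 / −0.01 | 5.2% / 5.3% | 0.01 / −0.01 | 4.8% / 4.8% |
| 24-month value, control arm only | 0.07 / 0.06 | 5.5% / 6.0% | 0.00 / 0.00 | 4.4% / 4.2% |
| 24-month value, opposite by arm | 0.10 / 0.09 | 6.9% / 7.3% | 0.00 / 0.00 | 4.5% / 4.7% |
| Unseen 36-month value, opposite by arm | 0.31 / 0.22 | 28.5% / 22.1% | 0.26 / 0.17 | 21.6% / 15.3% |

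Under random opt-in the empirical standard error is 0.223 / 0.182 for extension-only and 0.219 / 0.176 for all randomised, so including everyone loses no precision. In the fourth setting with a true effect of 0.5 SD, and with the bias running against the effect, power is 37% / 54% for extension-only against 54% / 74% for all randomised.

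**The case against.** The best defence is that the extension is optional, separately consented and openly described as restricted, and that the trial's main claims do not rest on it. That stands: the primary and key secondary endpoints are at 12 months.

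Three stronger readings are tempting, and the documents do not support them.

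- *The 36/48-month results are biased.* A reader might infer this from the loss of randomisation. But random opt-in, or the same dependence in both arms, gives essentially no bias under the null, and the documents say nothing about who opts in. The unadjusted figure of 0.29 SD also overstates the case, since SAP 7.3 adjusts for baseline.
- *Including everyone costs nothing and restores intention to treat.* It does not. The estimate is near zero in step 3 because opt-in was made to depend only on observed 24-month values. The last row of the table shows the bias reduced, not removed. And because closed-loop participants who decline stop closed loop, modelling them from earlier data estimates the effect had they stayed on it, not the effect of the assignment as actually followed.
- *The same model serves every outcome.* It does not. HbA1c below 7.5% uses repeated-measures logistic regression; if fitted by GEE, which Protocol 14.5 names for safety events, it is not valid under missing at random without weighting. Hypo- and hyperglycaemia metrics may be analysed non-parametrically (SAP 5.1, 7.3). Questionnaires use a linear model at each time point (SAP 15.1). Safety events after month 24 cannot be recovered from earlier visits.

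Nor does the point call for a particular covariance structure. HbA1c and insulin metrics have 16 post-baseline visits, so a full unstructured matrix would have 16 × 17/2 = 136 parameters from about 96 participants.

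**Conclusion.** The concern holds as an inconsistency in the plan and a risk of selection bias in the extension comparisons. SAP 4, 5.1 and 7.3 condition on a post-randomisation choice whose consequences differ by arm, against the stated principle in SAP 5.1 and Protocol 14, the cohort in SAP 5.2 and the missing-data rule in SAP 7.5.

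Under the assumed opt-in patterns that depend on the 24-month value, the baseline-adjusted bias is about 0.02-0.25 SD. It is about zero when all randomised participants' data to month 24 enter the likelihood model. These sizes rest on assumed opt-in rates, mechanisms and correlations. If entry depends on later, unseen values, the remedy helps only in part.

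**What to change.** For continuous repeated outcomes (fasting C-peptide/glucose, HbA1c, CGM, insulin and BMI):

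1. Delete the extension-only restriction in SAP 4, 5.1 and 7.3. Fit the 36/48-month direct-likelihood mixed model to all randomised participants with any post-baseline data, so that non-entrants contribute what they have to month 24. The rule against imputing CGM data is no obstacle, because direct likelihood imputes nothing.
2. Report the extension-only result as a sensitivity analysis.
3. Report opt-in by arm, with entrants' and non-entrants' 24-month characteristics.
4. Add a sensitivity analysis that departs from missing at random. Routine clinical data on non-entrants (Protocol 6.3 and 10.2) could inform it for HbA1c, BMI and insulin dose where permission has been given.
5. State that the main extension analysis assumes missing at random given data to month 24, and estimates the effect had participants continued in their allocated arm.

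Specify separately how selective entry is handled for binary HbA1c, any outcome analysed non-parametrically, questionnaires and safety events after month 24.

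The cost is SAP wording and a few extra analyses, with no new data collection. The price is the missing-at-random assumption and a hypothetical rather than treatment-policy estimate, both of which must be declared.

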### 5.2 Analysis Cohorts

- All randomized participants will be analyzed for the Intention-to-Treat (ITT) Analysis. All randomized subjects with at least one CGM reading will be included in CGM analyses.
- Safety outcomes will be reported for all enrolled participants, irrespective of whether the study was completed.
- A per-protocol analysis restricted to participants:

F:\user\Diabetes Studies\JDRFAPP\Protocols\APCam Newly Diagnosed - CLOuD\Statistics\Electronic Binder\4. SAP\CLOuD SAP V2.0 4-4-19.docx

167           ➤ in the CL group who used the CL system at least 60% of the time  
 168           ➤ in the MDI group who do not start insulin pump therapy

169       will be conducted at 12 and 24 months post diagnosis for:  
 170           ➤ the primary outcome (C-peptide AUC)  
 171           ➤ HbA1c  
 172           ➤ percentage of time with sensor glucose levels in the target range (3.9-10.0  
 173           mmol/L).

174       Additionally, per-protocol analyses also will be conducted for HbA1c and the percentage of time  
 175       spent in the target range at 36 and 48 months.

176       The per-protocol analyses for the percentage of time in the target range will be done separately at  
 177       each time point, so the analyses at 24, 36, and 48 months will not involve pooling CGM data at  
 178       12 months too. The per-protocol analyses will only be performed if at least 5% of the  
 179       participants do not meet the criteria above to be included in the analysis.

## 180       **6 Primary Analysis**

### 181       **6.1 Out Of Window Visits**

182       All MMTTs occurring between 300 and 420 days after the diagnosis date will be included in the  
 183       primary analysis. Any MMTTs occurring outside this window will be excluded.

### 184       **6.2 Statistical Methods**

185       The values obtained at 12-months post-randomization for log(C-peptide AUC+1) for the CL and  
 186       MDI arms will be compared using a linear model adjusting for baseline log(C-peptide AUC+1),  
 187       gender, presence or absence of DKA at diagnosis, and age as fixed effects and clinical site as a  
 188       random effect. The mean adjusted difference between treatment groups and the corresponding  
 189       95% confidence interval from the linear model will be reported. If residual values from the  
 190       regression model have a skewed distribution then an appropriate alternate transformation or a  
 191       nonparametric analysis based on ranks will be performed.

192       Per the protocol, any of the following variables may also be included in the model as fixed  
 193       effects to assess for the presence of confounding:

- 194           • HbA1c levels
- 195           • BMI z-score
- 196           • Race/ethnicity

197       Imbalances between groups in other important covariates are not expected to be of sufficient  
 198       magnitude to produce confounding. However, the presence of confounding will be evaluated in  
 199       the primary analysis by including any other factors potentially associated with the outcome for  
 200       which there is an imbalance between groups.

201       The primary analysis will be a single comparison and no attempt will be formally made to  
 202       control the overall type I error rate. A 5% significance level will be used to declare statistical  
 203       significance for the primary comparison.

F:\user\Diabetes Studies\JDRFAPP\Protocols\APCam Newly Diagnosed - CLOuD\Statistics\Electronic Binder\4. SAP\CLOuD SAP V2.0 4-4-  
 19.docx

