## 3 Sample Size

Assuming a mean area under the meal stimulated C-peptide curve of 0.37 pmol/ml for the control group based on the lower 90% confidence limit from previous data, a 50% increase in the intervention group gives  $0.37 \times 1.50 = 0.555$  pmol/ml. After a  $\ln(x+1)$  transformation, the mean values in the control and treatment groups are 0.315 and 0.441, respectively, giving a treatment effect of  $0.441 - 0.315 = 0.126$ . The treatment effect of 0.126 with a standard deviation of 0.18 requires 44 subjects per group at 90% power for a two sided-test at the 0.05 level. Allowing for 10% loss to follow up means we would need a total of 96 randomized participants (48 per group).

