### 13 Multiple Comparisons/Multiplicity

In this study, the primary analysis will be a single comparison of C-peptide AUC between the two treatment arms. The primary outcome will be tested at  $\alpha=0.04$ .

For the secondary analyses, the following outcomes will be considered key endpoints:

- Percent time in the target range (3.9-10.0 mmol/L)
- HbA1c
- Percent time below 3.9 mmol/L

These three endpoints will be tested in a hierarchical fashion in the order listed above. If C-peptide AUC is significant at  $\alpha=0.04$ , then they will be tested at  $\alpha=0.05$ . Otherwise, they will be tested at  $\alpha=0.01$ .

For all other secondary endpoints, the false discovery rate (FDR) will be controlled using the adaptive Benjamini-Hochberg procedure. The FDR will be calculated separately within each of the following categories:

- Secondary CGM Metrics
- Secondary Insulin Metrics
- Secondary HbA1c Metrics
- Secondary Clinical Metrics
- Subgroup Analyses and Sensitivity Analyses
- Per-Protocol Analyses
- Questionnaires

Due to the small number of subgroup analyses and sensitivity analyses, these will be combined into a single category. No adjustments for multiple comparisons will be done for safety outcomes.

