#### 14.5 Statistical methods

The respective values obtained during the 24-month randomised interventions and the extension phase, contrasting the closed loop against usual care will be compared using an ANCOVA model adjusting for gender, presence or absence of DKA, age and baseline log(C-peptide+1). Primary and secondary analyses will also be conducted to adjust for the baseline C-peptide and HbA1c levels, and by age, BMI, z-score, gender and race/ethnicity, as appropriate. A centre-effect will be explored in the analyses by evaluating for interaction between centre and treatment group on outcome. Secondary per protocol analyses will be conducted. Analyses will be carried out at month 24 and month 48 post-diagnosis.

205761\_Protocol\_V8.0\_10 September 2019

Primary analysis will be a single comparison and no attempt will be formally made to control the overall type I error rate for the secondary outcomes. For non-normally distributed parameters transformation or nonparametric analyses will be used. A 5% significance level will be used to declare statistical significance for the primary comparison.

Severe hypoglycaemic events and ketone-positive hyperglycaemia will be tabulated in each treatment group, which will be compared using repeated measures logistic regression (generalised estimator equation).

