## 14.7 Sample size and power calculations

The primary analysis will compare the difference between groups in the levels of the 2-hour AUC-mean using the  $\ln(\text{mean C-peptide}+1)$ . The residual standard deviation of the  $\ln(x+1)$  transformed C-peptide AUC analysis of covariance is referred to by TrialNet (Lachin 2011) as the root mean squared error (RMSE). The back-transform,  $\exp(y) - 1$ , of the mean of the transformed values is referred to by TrialNet as the geometric-like mean. In the DirecNet/TrialNet new onset studies (Lachin 2011), the point estimate for RMSE was 0.18 (transformed scale) and was used in the power calculations. As in the TrialNet sample size calculations, a 50% improvement was assumed in the geometric-like mean C-peptide AUC. The sample size depends on the geometric-like mean value in the control group. The original TrialNet sample size calculations assumed a value of 0.37 pmol/ml for the control group based on the lower 90% confidence limit from previous data (Lachin 2011). The present power calculation applied the same value. A 50% increase in the intervention group of the geometric-like mean C-peptide AUC gives  $0.37 \times 1.50 = 0.555 \text{ pmol/ml}$ . After  $\ln(x+1)$  transformation, the mean values in the control and treatment groups are 0.315 and 0.441 (transformed scale), respectively, the treatment effect is  $0.441 - 0.315 = 0.126$ . The treatment effect of 0.126 with a standard deviation of 0.18 requires 44 subjects per group at 90% power for a two sided-test at the 0.05 level. Allowing for 10% loss to follow up means we would need a total of 96 randomised participants (48 per group).

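### The primary C-peptide comparison has two significance levels, 5% in SAP 6.2 and protocol 14.5 and 4% in SAP 13, so its success rule is undefined for p-values between 0.04 and 0.05

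*Combined protocol and SAP*

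**What the plan says.** **Level for the primary.** SAP 6.2 (Statistical Methods, under Primary Analysis) says that the plan will not formally try to "control the overall type I error rate. A 5% significance level will be used to declare statistical" significance for the primary comparison. It reports a 95% confidence interval. Protocol 14.5 gives the same level: "A 5% significance level will be used to declare statistical significance for the primary comparison". SAP 13 (Multiple Comparisons/Multiplicity) gives a different one: "The primary outcome will be tested at $\alpha=0.04".

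**What follows the primary.** SAP 13 tests time in range, HbA1c and time below 3.9 mmol/L in that order. The level is 0.05 if C-peptide is significant at 0.04, and 0.01 otherwise. SAP 7.4 runs the 6-month C-peptide comparison only after a significant primary. SAP 12 makes the reading of the centre-by-treatment interaction depend on the same result.

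**Error control.** Protocol 14.5 says that "no attempt will be formally made to control the overall type I error rate for the secondary outcomes". SAP 6.2 makes the statement without limiting it to secondary outcomes. SAP 13 nevertheless sets out a procedure that covers the primary and the three key secondaries.

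**Sample size.** SAP 3 says the assumed effect "requires 44 subjects per group at 90% power for a two sided-test at the 0.05 level", and protocol 14.7 repeats the calculation. SAP 5.1 states: "All p-values will be two-sided".

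**The concern.** A confirmatory trial needs one rule, fixed in advance, for calling its primary result positive. Here a p-value between 0.04 and 0.05 is a success under SAP 6.2 and protocol 14.5 and a failure under SAP 13. In that zone the reported 95% interval would exclude zero while SAP 13 called the result non-significant.

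The conflict spreads to later steps. The same p-value sets the key secondaries at 0.05 or 0.01 and decides whether the 6-month test is run. In an open-label trial, the choice of rule could be made after the result is known.

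Error control is also at stake. The 0.01 fallback is paid for by testing the primary at 0.04. If the primary is declared at 0.05 and the fallback is kept, the total can exceed 5%.

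**Working it through.** **Inputs.** Effect 0.126 and SD 0.18 on the ln(x+1) scale, 44 per arm, 90% power, two-sided 0.05, 10% loss, 48 randomised per arm (SAP 3, protocol 14.7). Primary level 0.05 (SAP 6.2, protocol 14.5) or 0.04 (SAP 13). Fallback level 0.01 (SAP 13).

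**1. The plan's own figure.** The standardised effect is 0.126/0.18 = 0.70. With 44 per arm the standard error is 0.18 × √(2/44) = 0.0384, so the noncentrality is 0.126/0.0384 = 3.28. The two-sample t-test at two-sided 0.05 has power 90.1%. The stated 44 per arm is reproduced.

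**2. The zone of conflict.** With 44 per arm and SD 0.18, the smallest significant difference is 0.0763 at 0.05 and 0.0800 at 0.04. Observed differences between these two values get opposite verdicts. The probability of landing there is 0.05 − 0.04 = 1% under the null. Under the design effect it is 90.1% − 88.3% = 1.8%.

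**3. Familywise error.** The key secondaries are tested in order, so under the global null a false claim needs either the primary or the first key secondary to be rejected. If the two are independent:

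- SAP 13 alone: 1 − (1 − 0.04)(1 − 0.01) = 0.0496. The upper bound is 0.04 + 0.01 = 0.05.
- Primary at 0.05 with the 0.01 fallback kept: 1 − (1 − 0.05)(1 − 0.01) = 0.0595. The upper bound is 0.05 + 0.01 = 0.06.

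The documents give no correlation between the two test statistics, so it was varied by simulation (4 million draws of two correlated normal statistics, two-sided tests):

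| Correlation | SAP 13 alone | 0.05 primary + 0.01 fallback |
|---|---|---|
| 0 | 4.96% | 5.95% |
| 0.3 | 4.89% | 5.88% |
| 0.5 | 4.75% | 5.71% |
| 0.8 | 4.36% | 5.32% |
| 0.9 | 4.14% | 5.11% |

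The last row was run at −0.9; with two-sided tests the sign does not matter.

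**4. Power at 0.04** (two-sample t-test, same effect and SD):

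| Analysed per arm | Power at 0.05 | Power at 0.04 |
|---|---|---|
| 43 (48 × 0.9 = 43.2) | 89.4% | 87.5% |
| 44 | 90.1% | 88.3% |
| 48 | 92.4% | 90.9% |

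Reaching 90% at 0.04 takes 46 per arm by the normal approximation or 47 by the t-test, against 44 in the plan.

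**The case against.** **SAP 13 is the dedicated multiplicity section, so it governs.** It is sound taken alone, and it is probably the intended scheme. But SAP 6.2 is the dedicated primary-analysis section and is just as explicit. The protocol agrees with SAP 6.2, and the current protocol (V8.0, 10 September 2019) is later than the SAP (V2.0, dated 4-4-19 in its file footer). The appendix also lists a multiple comparisons diagram, which could not be read here. It may show which rule was meant, but it cannot remove the sentence in SAP 6.2.

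**The zone is narrow and the 6% is a worst case.** Both points stand. The zone carries 1% to 2% probability. The excess error arises only if the 5% rule of one section is joined to the fallback of another, and it shrinks as the correlation grows. It stayed above 5% at every correlation tried.

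**A reader might infer that the trial is underpowered.** The documents do not support that. The change is about two points at 44 per arm. SAP 5.1 includes all randomised participants in the primary analysis, and SAP 6.3.1 uses direct likelihood for missing 12-month values, so participants with earlier data contribute something. If all 48 per arm contribute fully, power at 0.04 is 90.9%. Nor is the rounding in the loss allowance (44/0.9 = 48.9 against 48 per arm) evidence of a problem: it is one patient per arm and has nothing to do with the two levels.

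**A reader might also infer that the 95% interval is wrong.** SAP 6.2 does not make the interval the decision rule, so it can stay as a descriptive summary.

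**Conclusion.** The point holds as an inconsistency between current sections. One primary test has two levels, no text gives precedence, and the outcome for p between 0.04 and 0.05 is undefined, along with the steps that depend on it. This part needs no assumption.

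The familywise figure of about 5.1% to 6.0% is conditional. It applies to the 5% rule combined with the 0.01 fallback, under the global null, for correlations from 0.9 to 0. SAP 13 on its own holds at most 5.0%.

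The power effect is secondary. It rests on the plan's effect and SD, and on how many participants contribute to the 12-month analysis: 87.5% to 90.9% at 0.04 for 43 to 48 per arm. It does not call for more participants. The point deserves correction because the success rule must be single and fixed in advance, not because the numerical effect is large.

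**What to change.** Before any unblinded analysis, state one primary level in SAP 6.2, SAP 13 and protocol 14.5. Two options are valid.

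- **(a) 0.04 throughout, keeping the SAP 13 scheme.** Change the level in SAP 6.2 and protocol 14.5. Note in SAP 3 and protocol 14.7 that the sample size was computed at 0.05, and that power at 0.04 is about 88% with 44 per arm (87.5% with 43, 90.9% if all 48 contribute). Leave the total at 96. The cost is a small drop in stated power.
- **(b) 0.05 for the primary, removing the 0.01 fallback.** Change SAP 13 so that the key secondaries are tested in order at 0.05 only after a significant primary. The sample-size sections stay as they are. The cost is that a failed primary leaves no formal test of the key secondaries.

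Under either option, narrow the statements on uncontrolled type I error in SAP 6.2 and protocol 14.5 to outcomes outside the primary and key secondaries. They should not simply be deleted: under SAP 13 the other secondaries have only false discovery rate control within categories, and safety outcomes have no adjustment. Under (a), a 96% interval beside the 95% one is optional.

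No extra participants or data are needed. A SAP revision is required, and probably a protocol amendment. If that amendment counts as substantial, protocol section 20 requires ethics and regulatory approval before it takes effect.
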